### Sample size calculation for clinical outcome

FFR-based treatment has proven to be superior to standard (based on angiography only) treatment by reducing the occurrence of MACE in the long-term [35]. Yet angina relief (an important determinant of quality of life in patients with ischemic heart disease) was not ameliorated by FFR guidance in a recent trial [7]. Thus, the FORZA trial aims to test if FD-OCT guidance may help to improve the clinical management of patients with ischemic heart disease and inconclusive results at coronary angiography. Since hard clinical endpoints are expected to have low frequency and PCI (especially in patients with good prognosis) is performed with the aim of improving the quality of life by eliminating angina and improving heart function, the occurrence of significant residual angina (<90 score at SAQ angina frequency scale) at 13 months has been considered as the primary endpoint.

For sample size calculations, we focused our attention on the clinical outcome at 13 months (a timepoint chosen assuming that most of patients had completed their 12-month double antiplatelet therapy one month before). Then, based on the FAME trial [7], we anticipate 20% of patients will be suffering from persistent angina at follow up in the FFR guidance group. Thus, 20% of patients are expected to have reached the primary endpoint at 13 months in the FFR guidance group. For the present study, we hypothesize that FD-OCT guidance could be able (due to the treatment of a greater number of stenoses and the optimization of stenting procedures which may reduce the rate of untreated angina-causing lesions) to reduce the occurrence of the primary endpoint by 50%. As a consequence, a total number of 400 patients (200 randomized to FFR guidance and 200 to FD-OCT guidance) has been calculated to be needed with an alpha error of 5% and a beta error of 20%.

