This sample size is also suitable to satisfy the secondary endpoint of the study, represented by a combination of MACE and/or relief from angina at 13-month follow up. Indeed we assume to have a 5% rate of MACE in the FFR guidance group, in line with the rate observed in a previous study of patients with intermediate lesions treated on the basis of FFR [10]. Thus, combined with the 20% of patients suffering persistent angina at follow up in the FFR guidance group, 25% of patients are expected to have reached the secondary endpoint at 13 months in the FFR guidance group. Since we expect a significant reduction in angina but not in MACE occurrence in the FD-OCT patients, we assume a 50% reduction (exclusively due to angina relief) of the secondary endpoint in this group. As a consequence, a total number of 304 (152 randomized to FFR guidance and 152 to FD-OCT guidance) has been calculated to satisfy the secondary endpoint requirements, with an alpha error of 5% and a beta error of 20%.

Finally, since the sample size is strongly dependent on the rate of events observed in the reference group (and figures in the literature are highly variable), when the first 150 patients complete the 13-month follow up, an interim analysis will be performed and eventually an amendment with a novel sample sizing will be calculated in the case of >30% difference between expected and observed rates.

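### The composite endpoint's sample size assumes a 50% reduction, but the plan's own components give 40% (25% to 15%): 500 patients are needed, not 304, and 400 give 71% power

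*Protocol article*

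**What the plan says.** All the inputs are in the Protocol article, Sample size calculation for clinical outcome.

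- Angina, FFR arm: "20% of patients are expected to have reached the primary endpoint at 13 months in the FFR guidance group".
- Angina, FD-OCT arm: guidance by FD-OCT is hypothesised "to reduce the occurrence of the primary endpoint by 50" per cent, so from 20% to 10%.
- MACE, FFR arm: "we assume to have a 5% rate of MACE in the FFR guidance group".
- Composite, FFR arm: "25% of patients are expected to have reached the secondary endpoint at 13 months in the FFR guidance group". The 20% and the 5% are added, with no overlap between them.
- MACE, FD-OCT arm: "we expect a significant reduction in angina but not in MACE occurrence in the FD-OCT patients".
- Composite, FD-OCT arm: "we assume a 50% reduction (exclusively due to angina relief) of the secondary endpoint in this group".
- Resulting size, at 5% alpha and 20% beta: "a total number of 304 (152 randomized to FFR guidance and 152 to FD-OCT guidance) has been calculated".
- Adequacy of the planned 400 patients: "This sample size is also suitable to satisfy the secondary endpoint of the study".

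The section Study endpoints names this composite the first secondary endpoint. It adds that the composite becomes the primary endpoint if MACE rates differ between arms by more than 1% in absolute terms.

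**The concern.** The 50% reduction belongs to angina. In the composite calculation it is applied to the whole 25%, including the 5 percentage points of MACE that the plan expects not to change. A component that stays fixed dilutes the relative effect on the composite, so the composite cannot fall by the same proportion as angina when angina is the only part that moves.

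The plan therefore credits the composite with at least 80% power at 400 patients when its own assumptions do not support that. A non-significant composite could be taken as the result of an adequately powered comparison. The stake is higher than for an ordinary secondary endpoint because the plan's own rule can make this composite the primary one.

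**Working it through.** **Formula.** Two proportions, pooled variance under the null, 1:1 allocation, no continuity correction:

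n per arm = [1.960·√(2·p̄·(1−p̄)) + 0.842·√(p1(1−p1) + p2(1−p2))]² / (p1−p2)², with p̄ = (p1+p2)/2.

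The plan does not state whether alpha is one- or two-sided. Two-sided 5% reproduces its figures; one-sided would give 240 patients for the composite and 314 for the primary endpoint.

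**Step 1: reproduce the plan's figures.**

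- Primary endpoint, 20% vs 10%: p̄ = 0.15; (0.9897 + 0.4208)² / 0.10² = 198.96, so 199 per arm and 398 in total. The plan has 400.
- Composite as stated, 25% vs 12.5%: p̄ = 0.1875; (1.0819 + 0.4586)² / 0.125² = 151.87, so 152 per arm and 304 in total. This matches the plan exactly.

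The formula is therefore the plan's own, and 304 is correct for 25% versus 12.5%. The error lies in the 12.5%.

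**Step 2: derive the FD-OCT composite rate from the plan's components.**

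- Angina: 20% × (1 − 0.50) = 10%.
- MACE: unchanged at 5%.
- Composite, added as in the FFR arm: 10% + 5% = 15%.
- Relative reduction: (25 − 15)/25 = 40%.

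To reach 12.5% by angina alone under the same addition, angina would have to be 12.5% − 5% = 7.5%. That is a reduction of (20 − 7.5)/20 = 62.5%, not the 50% assumed for the primary endpoint.

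**Step 3: sample size for 25% vs 15%.**

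p̄ = 0.20; (1.1087 + 0.4724)² / 0.10² = 249.98, so 250 per arm and 500 in total.

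**Step 4: power at the sizes the plan mentions.**

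Power = Φ{[(p1−p2)·√n − 1.960·√(2·p̄·(1−p̄))] / √(p1(1−p1) + p2(1−p2))}

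| Composite rates | 152 per arm (304) | 200 per arm (400) |
|---|---|---|
| 25% vs 12.5% (as stated) | 80.0% | 89.6% |
| 25% vs 15% (from the components) | 58.8% | 70.7% |

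**Step 5: sensitivity to simple addition.** Suppose instead that angina and MACE occur independently in each arm (an assumption, not in the plan). The rates become 1 − 0.80 × 0.95 = 24% and 1 − 0.90 × 0.95 = 14.5%. The requirement is then 270 per arm (540 in total), and power at 400 is 67%. The conclusion does not depend on adding the rates without overlap.

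**Step 6: if the composite is promoted.** The trigger is a MACE difference above 1%, whereas the planning assumption is none. At a difference of exactly one point, with the control composite held at 25%, the FD-OCT rate is 14% if MACE favours FD-OCT and 16% if it favours FFR. Power at 400 is 79.5% and 60.7% respectively.

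**The case against.** Five points can be made for the plan.

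- **The trial size does not rest on this calculation.** The 400 comes from the angina endpoint, which reproduces at 199 per arm with 80% power. The 304 is below 400 and set nothing, and a secondary endpoint need not have 80% power. This stands, and it is why the correction is cheap. It does not rescue the statement that 400 is adequate for the composite at a 20% beta error.
- **The effect assumption is the sponsor's to choose.** If the 50% composite reduction is kept, 304 is right and 400 gives about 90% power. That is true in isolation. But the plan attributes the 50% solely to angina, and it has already fixed the angina effect at 20% to 10%. Keeping 12.5% means giving up one of those statements.
- **Overlap could produce 12.5%.** With 10% angina, 5% MACE and 2.5% of patients having both, the composite is 12.5%. So the figure is not strictly impossible. It would need half of the FD-OCT patients with MACE to have angina as well, while the FFR arm's 25% allows no overlap at all. Nothing in the plan supports such a difference.
- **The interim review could correct the size.** It reacts to a difference of more than 30% between expected and observed rates. A rate of 15% against an expected 12.5% differs by 2.5/12.5 = 20%, which is below that trigger. In any case the review would carry the inconsistent expected rate forward.
- **Over-reading of a null result is a prediction.** That is fair, since the document does not say how a null composite would be interpreted. The misstated power is an error regardless.

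**Conclusion.** The concern holds, and the calculation is wrong as written. On the plan's own inputs the composite falls from 25% to 15%, a 40% reduction. Detecting this with 80% power takes 500 patients, not 304, and the planned 400 give 71%.

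This rests on three things the plan states (angina halved from 20% to 10%, MACE unchanged at 5%, the two rates added) and on two-sided 5% testing, which is inferred because it reproduces both of the plan's sample sizes. No dropout allowance is stated, so none was applied. The primary endpoint's calculation is not affected.

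**What to change.** In Sample size calculation for clinical outcome:

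1. Replace the 50% reduction in the composite with a 40% reduction, from 25% to 15%.
2. Replace 304 (152 per arm) with 500 (250 per arm).
3. Replace the statement that 400 is adequate for the composite with one that 400 patients give about 71% power for it.

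If the sponsor does intend a 50% reduction in the composite, the text must instead say which of the angina, MACE or overlap assumptions differs from those now stated, and why.

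Simply labelling the composite as supportive would not be enough, because it would clash with the rule in Study endpoints that can make it primary. Beside that rule, state that the composite has about 71% power at 400 under the no-MACE-effect assumption.

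The cost is a few restated figures in the protocol. No analysis changes, and no extra patients are needed if the lower power is accepted and disclosed. Restoring 80% power for the composite would take 100 more patients (500 − 400).

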### Sample size calculation for peri-procedural management costs

The costs for each arm are anticipated to be the combination of diagnostic procedural costs, interventional procedures (eventually derived from the diagnostic ones) and costs related to events occurring during the follow up. On the basis of the NASCI study, we expect a 30% of PCI in the FFR-guided arm [17]. Contrastingly, according to our experience (three years FD-OCT experience at our institution, unpublished data), PCI is anticipated to be performed in about 50% of the FD-OCT-guided arm. Thus considering the mean costs of a FFR-guided PCI (3600€ for PCI + 940€ for the pressure wire + 170€ for adenosine = 4710€) and of an FD-OCT guided PCI (3600€ for PCI + 1600€ for the FD-OCT catheter = 5200€) and the costs of a coronary angiography with FFR (500€ for coronary angiography + 940€ for the pressure wire plus 170€ for adenosine = 1610€) and of a coronary angiography with FD-OCT (500€ for coronary angiography + 1600€ for FD-OCT catheter = 2100€) we expect an overall costs reduction of 30% in the FFR-guidance group compared to the FD-OCT guidance group. Assuming no occurrence, or at least a similar occurrence of MACE, or recurrence of angina at 30 days follow up in both arms, we expect an overall 30% reduction of costs at 30 days follow up in the FFR-guided arm. A total number of 220 patients (110 randomized to FFR guidance and 110 to FD-OCT guidance) with an alpha error of 5% and a beta error of 20% has been calculated to be needed to test this hypothesis.

### Study limitations

The major anticipated limitation of the present study is that it is an open-label and not a double-blinded trial. The treating physicians cannot be blinded since a FFR-guided procedure is fairly different from an FD-OCT-guided PCI.

## Trial status

The trial is in the patient recruitment phase, started on April 2013.

## Abbreviations

AICL: angiographically- intermediate coronary lesions; AS%: percentage of area; dRLA: distal reference lumen area; FD-OCT: frequency domain optical coherence tomography; FFR: fractional flow reserve; MACE: major cardiovascular event; MI: myocardial infarction; MLA: minimal lumen area; mRLA: mean reference lumen area; PCI: percutaneous coronary intervention; pRLA: proximal reference lumen area; SAQ: Seattle angina questionnaire; TVR: target vessel revascularization.
